**Aims:**

This study was a part of a multi-center study designed to evaluate the diagnostic accuracy of  $^{99m}\text{Tc}$ -3PRGD2 imaging in lung cancer patients. The aim of this sub-topic was to compare  $^{99m}\text{Tc}$ -3PRGD2 imaging with  $^{99m}\text{Tc}$ -MDP bone scan in evaluation of bone metastasis in lung cancer patients.

**The medical centers and facilities:**

| Centers                                                                        | SPECT system          |
|--------------------------------------------------------------------------------|-----------------------|
| The 1 st Affiliated Hospital of Fujian Medical University, Fuzhou   | GE Infinia Hawkeye    |
| Beijing Tongren Hospital, Beijing                                              | GE Infinia Hawkeye4   |
| The 1 st Affiliated Hospital of Nanjing Medical University, Nanjing | Siemens Symbia T6     |
| Peking Union Medical College Hospital, Beijing (the organizer center)          | Philips Precedence 16 |

**Estimated Enrollment:** 40

**Study Start Date:** February 2011

**Estimated Study Completion Date:** March 2014

**Introduction:**

Integrin is mainly involved in the cell-cell and cell-matrix interactions. Integrin  $\alpha_v\beta_3$ , an important member of the integrin family, is highly relevant to neoplastic angiogenesis, invasion, and metastasis. It is not expressed at all or expressed at a very low level on the quiescent endothelium and other normal tissues. Therefore, the integrin  $\alpha_v\beta_3$  receptor may be a promising target in the diagnosis, evaluation, and treatment of malignancies, serving as a tumor-specific agent for single photon emission computed tomography (SPECT).

The tri-peptide sequence of arginine-glycine-aspartic acid (RGD), especially in

cyclic form, has shown high affinity in binding with the receptors of integrin  $\alpha_v\beta_3$ .  $^{99m}\text{Tc}$ -3PRGD2 could be easily prepared and exhibited excellent in vivo behaviors in animal models. No adverse reactions are observed in animal models to date.

For further interest in clinical translation of  $^{99m}\text{Tc}$ -3PRGD2, this study was designed to investigate the value of  $^{99m}\text{Tc}$ -3PRGD2 in assessment of bone metastasis in lung cancer patients, which was compared with  $^{99m}\text{Tc}$ -MDP.

## Methods

A single dose of 11.1 MBq/kg body weight  $^{99m}\text{Tc}$ -3PRGD2 will be intravenously injected into the patients, and then whole body planar scan (10 cm/min) and chest SPECT imaging (zoom  $\times 1$ , 30 sec/frame/ $6^\circ$ ) will be performed at dual time-points of 1 h and 4 h.  $^{99m}\text{Tc}$ -MDP whole body imaging will be done for comparison within 1 week before or after  $^{99m}\text{Tc}$ -3PRGD2 imaging. Consensus reading of  $^{99m}\text{Tc}$ -3PRGD2 and  $^{99m}\text{Tc}$ -MDP images will be performed on the same workstation by three experienced nuclear medicine physicians blind to the history and pathological diagnosis. The sensitivity, specificity, accuracy, positive predictive value, and negative predictive value will be employed to determine the efficacy of  $^{99m}\text{Tc}$ -3PRGD2 imaging for the diagnosis of bone metastases.

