## Eligibility

### Inclusion Criteria:

1. Males and females,  $\geq 30$  years old
2. Patients suspected with primary lung cancer with thoracic CT
3. The lung cancer will be histologically confirmed or results of histology will be available.
4.  $^{99m}\text{Tc}$ -MDP whole body scan will be performed within 1 week before or after  $^{99m}\text{Tc}$ -3PRGD2 imaging.
5. The bone lesion will be confirmed from at least 2 imaging modalities (SPECT/CT/MRI/ $^{18}\text{F}$ -FDG PET-CT) and 6-month follow-up.

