### Flow Chart

| RESEARCH PROCESS                         | V1 | V2                                  | V3                                                                 | V4
(Surgery) | V5
(Follow-up) |
|------------------------------------------|----|-------------------------------------|--------------------------------------------------------------------|-----------------|-------------------|
| Window period                            |    | Within two weeks before the surgery | Within one week before/after the $^{99m}\text{Tc}$ -3PRGD2 imaging |                 | Every 3-6 months  |
| Inclusion / Exclusion criteria           | X  |                                     |                                                                    |                 |                   |
| Signed the Informed Consent              | X  |                                     |                                                                    |                 |                   |
| Medical history / Concomitant diseases   | X  |                                     |                                                                    |                 |                   |
| CT, MRI, PET/CT                          | X  |                                     |                                                                    |                 |                   |
| Tumor markers and other laboratory tests | X  |                                     |                                                                    |                 |                   |
| $^{99m}\text{Tc}$ -3PRGD2 SPECT          |    | X                                   |                                                                    |                 |                   |
| $^{99m}\text{Tc}$ -MDP whole body scan   |    |                                     | X                                                                  |                 |                   |
| Adverse events                           |    | X                                   |                                                                    |                 |                   |
| Surgical records and pathology results   |    |                                     |                                                                    | X               |                   |

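### The stated scan windows do not rule out an MDP scan up to six days after surgery, while 3PRGD2 in operated patients is always pre-operative

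*Protocol*

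**What the plan says.** The Protocol's aim is to compare 3PRGD2 imaging with the MDP bone scan for bone metastasis in lung cancer. The timing of the two scans is fixed in three places.

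- **Flow Chart, V2 (3PRGD2):** "Within two weeks before the surgery".
- **Flow Chart, V3 (MDP):** "Within one week before/after the" 3PRGD2 scan. The cell contains no limit relative to surgery.
- **Methods:** MDP "whole body imaging will be done for comparison within 1 week before or after" 3PRGD2 imaging.
- **Inclusion criterion 4:** the MDP "whole body scan will be performed within 1 week before or after" 3PRGD2 imaging.

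Surgery is V4, the column after MDP, and the row "Surgical records and pathology results" is marked only there. Images are read in consensus by three "physicians blind to the history and pathological diagnosis". Inclusion criterion 5 sets the reference standard: "The bone lesion will be confirmed from at least 2 imaging modalities", together with 6-month follow-up. Estimated enrolment is 40.

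**The concern.** The two scans are anchored to different events: 3PRGD2 to the operation, MDP only to 3PRGD2. Where 3PRGD2 is done in the last few days before surgery, the one-week allowance for MDP runs past the operation. The reverse cannot happen, because in operated patients 3PRGD2 must come first.

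The possible error therefore runs one way. If an operation produced uptake on a later MDP scan and that uptake was called metastatic, the reference standard would in due course classify the site as benign and the call would count as an MDP false positive. Readers who do not know the history could not allow for the operation. MDP specificity and positive predictive value could then look worse for a reason unrelated to the tracer. The comparison with MDP is the stated aim of this sub-study, and with 40 patients a few such calls would show.

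**Working it through.** The Protocol gives no figure of its own on this point, so there is nothing to reproduce. The check is an enumeration of the permitted days.

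**Inputs**
- Surgery is day 0.
- 3PRGD2 is on day −d, with d = 1 to 14 (Flow Chart, V2).
- MDP is at offset o = −7 to +7 days from 3PRGD2 (Methods; inclusion criterion 4; Flow Chart, V3).

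**Latest permitted MDP.** MDP falls on day o − d. The maximum is 7 − 1 = 6, so MDP may be as late as day +6.

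**When MDP can be post-operative.** This requires o > d. Since o is at most 7, it is possible only for d = 1 to 6.

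**Permitted day pairs**
- All pairs: 14 × 15 = 210.
- Pairs with o > d: 6 + 5 + 4 + 3 + 2 + 1 = 21.
- Share: 21/210 = 10.0%.
- In continuous time: (7 × 7/2)/(14 × 14) = 24.5/196 = 12.5%.
- Only pairs in which MDP is on a later day than 3PRGD2: 21/(14 × 7) = 21/98 = 21.4%.
- If MDP also had to precede surgery: 0 of 210 post-operative.

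These are shares of what the text allows. They are not predicted frequencies.

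**Does the visit order close the gap?** Set side by side, the column order V2, V3, V4 suggests both scans before surgery. But the V3 window lets MDP come before 3PRGD2, so column order is not strictly calendar order. A site scanning MDP on day +3, with 3PRGD2 on day −2, is 5 days from 3PRGD2 and meets inclusion criterion 4 and the V3 cell, though it departs from the column order.

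**Illustrative size.** The following are assumptions, not Protocol figures: all day pairs equally likely; a share s of patients operated on, 25% to 100%; a share q of post-operative MDP scans wrongly called positive, 25% to 100%; all 40 patients otherwise true negatives, analysed by patient. Extra MDP false positives = 40 × s × 0.10 × q.

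| s | q | Extra false positives | Loss of specificity (points) |
|---|---|---|---|
| 25% | 25% | 0.25 | 0.6 |
| 50% | 50% | 1.0 | 2.5 |
| 100% | 50% | 2.0 | 5.0 |
| 100% | 100% | 4.0 | 10.0 |

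If sites follow V2-V3-V4, every row becomes zero.

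**The case against.** The strongest reply is that the Flow Chart already answers the question: MDP is V3, surgery is V4, and the natural reading is that both scans precede the operation and only their mutual order is free. On that reading a clarifying phrase is missing and nothing more. This carries weight. It shows that a post-operative MDP scan is not planned. It does not show that one is excluded, because none of the three statements of the MDP window mentions surgery and the visit numbers are not strictly chronological.

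Several stronger readings are tempting, and the documents do not support them.

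- **That MDP will show post-operative false positives.** The Protocol gives no rate of such uptake, no share of patients operated on, and does not make surgery a condition of entry. The text supports only that it could happen.
- **That the surgery is thoracic, so that rib or sternal uptake is to be expected.** The Protocol says only surgery. The site is an inference from the disease.
- **That 43% of MDP scans are at risk.** 6/14 = 43% is the share of permitted 3PRGD2 days on which some later MDP day could fall after surgery. It is not a share of scans.
- **That a specificity of 80% would appear as 76% to 70%.** This takes 10% to 25% of scans as post-operative and half of those as misread: 0.80 × (1 − 0.05) = 0.76 and 0.80 × (1 − 0.125) = 0.70. None of these inputs is in the Protocol. The calculation also treats every patient without metastasis as operated on; with half operated on, the range is 78% to 75%.
- **That treatment starting between the scans adds to the same bias.** MDP may precede or follow 3PRGD2, so treatment could affect either scan. The Flow Chart also places subsequent treatment at V5.

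Nor is the blinding a fault. It applies to both tracers and protects the reading. It matters here only because it prevents readers from correcting for an operation they do not know of.

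**Conclusion.** The point holds as a gap in the timing rules, not as a demonstrated bias. The written windows permit MDP up to day +6 and never permit 3PRGD2 after surgery, so any resulting error would fall on the comparator alone and favour 3PRGD2.

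Its likely size cannot be fixed from the Protocol. The illustration spans 0.6 to 10 points of MDP specificity, and its upper end needs every patient operated on and every post-operative scan misread. It is worth correcting because it bears on the study's stated comparison, can run in only one direction, and is cheap to remove. An analysis plan can set affected pairs aside, but it cannot prevent them from arising under the Protocol's windows.

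**What to change.** 1. Reconcile Methods, inclusion criterion 4 and the V2, V3 and V4 columns of the Flow Chart so that they state consistently how MDP timing relates to surgery. The choice of schedule is for the sponsor and the investigators; the need is that the three places agree.
2. Record the dates of both scans and of any operation. Restrict the main paired comparison to pairs with no surgery between the two scans, and report the remaining pairs in a sensitivity analysis. This definition may sit in the Protocol or in the analysis plan.

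The cost is a line in the timing text and a line in the definition of the analysis set. The downside is that a few pairs may leave the main set, which matters somewhat with 40 patients; the sensitivity analysis keeps them in view.

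### The reading rule masks the panel to history and pathology but does not require each tracer to be read without knowledge of the other, so the comparison is open to cross-reading bias.

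*Protocol*

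**What the plan says.** The Aims section makes the comparison the purpose of this sub-study: "The aim of this sub-topic was to compare" the two tracers "in evaluation of bone metastasis in lung cancer patients". Methods pairs the scans within patients, since MDP "whole body imaging will be done for comparison within 1 week before or after" the 3PRGD2 scan.

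A single sentence in Methods governs reading. It opens "Consensus reading of", names both tracers, and continues: "images will be performed on the same workstation by three experienced nuclear medicine physicians", who are "blind to the history and pathological diagnosis". It therefore fixes four things: consensus reading, one panel of three, one workstation, and masking to two items. The other tracer's scan is not among the masked items. The protocol gives no separate sessions, reading order, interval or locking of calls. Nor does it say that the scans are read together.

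The next sentence lists the measures of 3PRGD2's efficacy: "The sensitivity, specificity, accuracy, positive predictive value, and negative predictive value will be employed".

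**The concern.** In a comparison of two tests on the same patients, the information on the difference lies in the discordant pairs, where one scan is called positive and the other negative. A reader who knows both scans is most likely to change those calls. A focus on MDP can prompt a closer search at the same site on 3PRGD2, and a cold 3PRGD2 scan can lead readers to dismiss an MDP focus. The Introduction presents the 3PRGD2 target as tumour-specific, so that scan may also reveal disease extent, which masking to history is presumably meant to withhold.

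Two results are at stake: the difference between the tracers, and the stand-alone accuracy of 3PRGD2. If MDP is in view, the second becomes the accuracy of 3PRGD2 read together with MDP, which answers another question. No statistical analysis of calls made with both scans in view can recover what the readers would have called from one scan alone.

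**Working it through.** **No figure to reproduce.** The protocol estimates an enrolment of 40 but gives no expected accuracy, discordance rate, significance level or power. Every rate below is an assumption, chosen to show how the mechanism works.

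**1. Effect on the difference.** Among patients with bone metastases, let p10 be the share called positive on 3PRGD2 and negative on MDP, and p01 the reverse. The true sensitivity difference is p10 − p01. If knowledge of both scans turns a share a of the first type and b of the second into agreement, then

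observed difference = p10(1 − a) − p01(1 − b).

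| p10, p01 (true difference) | a, b | Observed difference |
|---|---|---|
| 0.20, 0.10 (+0.10) | 0, 0 | 0.20 − 0.10 = +0.10 |
| | 0.3, 0.3 | 0.14 − 0.07 = +0.07 |
| | 0.5, 0.5 | 0.10 − 0.05 = +0.05 |
| | 0.5, 0 | 0.10 − 0.10 = 0 |
| | 0, 0.5 | 0.20 − 0.05 = +0.15 |
| 0.15, 0.15 (0) | 0.5, 0.5 | 0.075 − 0.075 = 0 |
| | 0.5, 0 | 0.075 − 0.15 = −0.075 |
| | 0, 0.5 | 0.15 − 0.075 = +0.075 |

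Symmetric influence shrinks the difference. One-sided influence can remove it, enlarge it, or create one in favour of either tracer. No influence means no bias.

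**2. Effect on precision, in one scenario.** Assume specificity 0.90 for 3PRGD2 and 0.65 for MDP, calls independent given true status, and 25 of the 40 patients free of bone metastasis. The discordant cells in those patients are 0.90 × 0.35 = 0.315 and 0.10 × 0.65 = 0.065, a difference of 0.25. Suppose a share c of both cells is revised to agree. The observed difference is 0.25(1 − c), and the last column gives the power of an exact two-sided 5% McNemar test.

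| c | Observed difference | Power, n = 25 |
|---|---|---|
| 0 | 0.250 | 0.422 |
| 0.1 | 0.225 | 0.364 |
| 0.3 | 0.175 | 0.236 |
| 0.5 | 0.125 | 0.104 |

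As c goes from 0 to 0.5, power falls from 0.303 to 0.050 with 20 bone-negative patients and from 0.524 to 0.168 with 30. Even at c = 0 power is below one half at n = 25, so much of the shortfall comes from the small sample and not from cross-reading.

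**3. Effect on 3PRGD2's own figures.** Add assumed sensitivities of 0.80 for 3PRGD2 and 0.85 for MDP. The discordant cells in patients with metastases are 0.20 × 0.85 = 0.17 (MDP positive only) and 0.80 × 0.15 = 0.12 (3PRGD2 positive only). The results below are for c = 0.1, 0.3 and 0.5.

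- 3PRGD2 calls move to MDP in both directions: sensitivity 0.80 + c(0.17 − 0.12) = 0.805, 0.815, 0.825; specificity 0.90 − c(0.315 − 0.065) = 0.875, 0.825, 0.775.
- Only missed lesions are revised upward: sensitivity 0.80 + 0.17c = 0.817, 0.851, 0.885.

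The gain in sensitivity is 3.4 times larger under the second rule (0.17 against 0.05 per unit of c). The result depends on which revision rule is assumed, and the protocol gives no basis for choosing one.

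**The case against.** A reader might infer that the panel is in fact unmasked to the other tracer and that the reported difference is therefore biased. The text does not support this. It neither requires nor rules out separate masked reading, and a panel that read the tracers weeks apart would comply equally well. The most that can be said is that the plan permits cross-reading.

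A reader might also fault the shared panel and workstation, or the lack of independence between the two calls. Neither is a defect. The same readers on the same display remove reader and display differences from a within-patient comparison, which helps when the four centres use four different SPECT systems. Calls on the same patient are correlated in any paired design, and a paired analysis allows for that.

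The strongest objection is that session order, interval and locking are often set in a statistical analysis plan or reading manual. The protocol is a short outline of one part of a larger study, and such a document may exist. That has force for the operational detail. It has less for the masking itself: Methods does state what the readers are blind to, and the list omits the comparator scan in a study whose aim is the comparison. The criticism is of the scope of a rule that the protocol chose to write.

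The illustrations are also fairly open to challenge. All their inputs are assumed, and the loss of power in step 2 arises only if both kinds of discordance shrink in proportion.

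**Conclusion.** The concern holds in a limited form. The stated masking is incomplete for a head-to-head comparison. It allows either scan to influence the call on the other, and so leaves both the comparison and the 3PRGD2 accuracy figures open to cross-reading bias. That bias is possible, not shown. Its size and direction are unknown, and the numerical examples show only that it could run either way or be absent. The conclusion rests on the wording of the one reading sentence and on the stated aim, not on those examples. It would fall away if another study document already requires each tracer to be read masked to the other. This is an inexpensive improvement worth making before images are read; the protocol does not show that the results are invalid.

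**What to change.** Amend the reading sentence in Methods along these lines: the same three physicians read the 3PRGD2 and MDP images in separate sessions, de-identified and in random patient order, with an interval between sessions, without access to the other tracer's images or calls; calls are locked before any joint review.

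An interval of a few weeks is a reasonable choice, but no figure in the documents dictates it. The essential clause is the one denying access to the other tracer's images and calls. A side-by-side read may follow as a labelled secondary analysis of what the two scans add to each other.

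The cost is a change of wording, a random reading list and a second session for the same panel. No extra patient, scan or staff is needed. The delay is short and fits within the 6-month follow-up that the inclusion criteria already require for confirming bone lesions.

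### The stated reader masking covers history and pathology, but not the other tracer's scan or the imaging and follow-up that settle bone status

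*Protocol*

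**What the plan says.** The protocol's Methods section gives one rule for reading the scans. A single panel reads both tracers by consensus, and this reading "will be performed on the same workstation by three experienced nuclear medicine physicians blind to the history and pathological diagnosis". The section mentions no other masking, no separate sessions, no reading order and no interval between the two reads.

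The two scans are paired within patient: MDP "whole body imaging will be done for comparison within 1 week before or after" the 3PRGD2 scan.

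The Inclusion Criteria separate two kinds of confirmation. Item 3 concerns the primary tumour: "The lung cancer will be histologically confirmed or results of histology will be available". Item 5 concerns bone: "The bone lesion will be confirmed from at least 2 imaging modalities", the choices being SPECT, CT, MRI and FDG PET-CT, together with six months of follow-up.

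The Flow Chart places CT, MRI and PET/CT at V1, 3PRGD2 SPECT at V2, the MDP scan at V3, surgical pathology at V4 and follow-up at V5.

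**The concern.** In a diagnostic comparison, masking protects the result only if it covers the information that decides the true status and, in a paired design, the competing test. Here the stated masking covers neither. Readers kept from the pathology report are kept from a result about the lung, while the rule is silent on the images and follow-up that determine whether a bone lesion counts as metastatic.

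Two effects are possible. A panel that knows the other tracer's scan can settle a borderline lesion by reference to it. That may pull the two tests together or, if the panel leans towards one tracer, push them apart. A panel that knows the CT, MRI or PET-CT findings would tend to read both tracers more accurately than either scan alone allows. The first effect touches the head-to-head comparison, the second mainly the absolute sensitivity and specificity. Once calls have been made with that knowledge, statistical analysis cannot recover the calls that would have been made without it.

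**Working it through.** The protocol gives no figure to reproduce on this point, so the check sets its sections side by side.

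**1. What the reads must support.** The Aims section states a comparison of 3PRGD2 with the MDP "bone scan in evaluation of bone metastasis in lung cancer patients". The consensus calls are the data for that comparison.

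**2. What the masking covers, against what matters for bone.**

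| Information | Role for bone lesions | Masking stated in Methods? |
|---|---|---|
| History | Clinical context | Yes |
| Pathological diagnosis | Concerns the lung cancer (Inclusion item 3; surgery visit V4) | Yes |
| CT, MRI, FDG PET-CT | Named among the modalities that confirm bone lesions (item 5) | No |
| Six-month follow-up | Part of the bone confirmation (item 5) | No |
| The other tracer's scan | The competing test in the same patient | No |

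Everything that item 5 uses to settle bone status, and the competing test, falls in the rows without stated masking. No other section of the protocol adds any.

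**3. Whether the information could be available at reading.** By visit order, CT, MRI and PET/CT (V1) precede both study scans (V2, V3). The MDP scan may fall up to a week before or after 3PRGD2, so either scan could be known when the other is read. The protocol gives no date for the reads, so availability of follow-up at reading can be neither shown nor excluded.

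**4. Why a paired comparison is exposed.** Let n be the number of patients with bone metastases by the reference, b the number of them called positive on 3PRGD2 only, and c the number called positive on MDP only. Then

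difference in sensitivity = (b − c) / n.

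Only discordant patients contribute, and these are the calls that knowledge of the other scan can change. Each call changed on one tracer moves the difference by 1/n. With an enrolment of 40, n cannot exceed 40, so in a per-patient analysis one changed call moves the difference by at least 1/40 = 2.5 percentage points, and by more if fewer patients have metastases. This shows how far a single call can move the result; it does not estimate the bias. In a per-lesion analysis the denominator would be the lesion count, which is not given.

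**5. Size and direction.** An estimate would need the prevalence of bone metastasis, the accuracy of each tracer, their agreement, and the share of calls altered by knowing the other images. The protocol gives none of these.

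**The case against.** The strongest reply is that silence is not permission. A reader might infer that the two tracers are read side by side, that the panel has CT, MRI and PET-CT in view, and that the comparison is therefore unblinded. The text supports none of these. One workstation fixes the hardware, not the session, the order or the display. With four SPECT systems from three vendors, it is most naturally a way to standardise viewing. Partial masking is stated, so calling the study unblinded would be wrong.

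The link from the V1 imaging to the bone reference is also not spelled out. A thoracic CT is needed for entry, so some of that imaging may be staging work-up. Masking to history might have been meant to include earlier imaging results. Session details may sit in a reading manual or in the parent multi-center study, neither of which is shown.

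A reader might also fault consensus reading itself. It is a recognised design with known limits; preferring a majority of three independent calls is a matter of choice. Attaching a figure to the bias would likewise only restate whatever counts were assumed.

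All of this limits the claim, but it does not close the gap. The protocol sets the masking rule in its own Methods, and a panel could follow that rule to the letter while knowing the other scan and the reference images. Masking is also a matter of trial conduct, so a later analysis plan cannot supply it.

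**Conclusion.** The point stands in this form: the protocol specifies no masking of either tracer's read to the other tracer, to CT, MRI or PET-CT, or to follow-up, and the masking it does specify misses the information that settles bone status. The plan as written therefore permits review bias in its central comparison. It does not establish that such bias will occur.

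The size and direction cannot be derived from the document. The conclusion rests on two readings of the text: that pathological diagnosis means the lung tumour's pathology, as Inclusion item 3 and the surgery visit indicate, and that history does not extend to prior imaging results. If the sponsor intended the wider meaning of history, part of the gap concerning CT, MRI and PET-CT would close, but masking to the other tracer and to follow-up would still be unstated.

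**What to change.** Amend the masking sentence in Methods to state that:

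- the same three readers read 3PRGD2 and MDP in separate sessions, in random patient order, with a washout interval between them;
- each session is masked to the other tracer's scan, to CT, MRI and PET-CT and to follow-up, in addition to history and pathology;
- the consensus call for each tracer is recorded and locked before any unmasking.

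Consensus reading may stay. Recording each reader's own call before discussion is optional.

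The cost is one additional reading session for about 40 patients by the same readers, with the work of preparing masked image sets. No patient procedure is added. The sponsor should also expect that apparent accuracy may be lower for both tracers than it would be with the other images in view.

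### The reader masking covers history and pathology but is not stated to cover the other imaging and follow-up that define bone status, so a compliant reading could be informed by part of the reference

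*Protocol*

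**What the plan says.** Under Methods, the 3PRGD2 and MDP images are read by consensus on one workstation by three nuclear medicine "physicians blind to the history and pathological diagnosis". That is the whole masking rule. Five accuracy measures, from sensitivity to negative predictive value, "will be employed to determine the efficacy of" 3PRGD2 imaging for bone metastases.

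The standard against which those measures are formed appears only under Inclusion Criteria, item 5: "The bone lesion will be confirmed from at least 2 imaging modalities", with SPECT, CT, MRI and FDG PET-CT as the admissible methods, "and 6-month follow-up". Bone histology is not required. The histology that the protocol does require is in item 3 and concerns the primary tumour: "The lung cancer will be histologically confirmed or results of histology will be available".

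The Flow Chart marks CT, MRI and PET/CT at V1, the 3PRGD2 scan at V2, the MDP scan at V3, surgical pathology at V4 and follow-up at V5. It gives "Medical history / Concomitant diseases" a row of its own, apart from the imaging row. The date of the consensus reading is not fixed anywhere.

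**The concern.** In a diagnostic accuracy study, the essential purpose of masking the readers is to keep the index reading independent of the reference. Here the pathology masking shields readers from the lung diagnosis. That suits the parent study's question of lung cancer detection, but it gives little protection for this sub-study's question, which is bone metastasis. The information that decides bone status is not named.

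A reader who knows that PET-CT or MRI has called a lesion malignant is drawn towards the same call on an equivocal tracer uptake, and the reverse holds for a lesion called benign. Either way, agreement with the reference rises. All five accuracy measures are built on that agreement. The results could then be reported as a blinded reading although nothing in the plan shielded the panel from what defines the truth. They would not describe a scan read without that other imaging.

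**Working it through.** The plan gives no figure to reproduce. Enrolment is 40, with no expected sensitivity or specificity and no precision target. The main check is therefore to set the sections side by side.

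| Information | Named in the masking rule (Methods)? | Part of the bone reference (Inclusion item 5)? | In existence when the tracers are read (Flow Chart)? |
|---|---|---|---|
| Medical history | Yes | No | Yes, V1 |
| Lung histology / surgical pathology | Yes | No | Surgical pathology at V4; depends on the reading date |
| CT, MRI, PET/CT | No | Yes | Yes, V1 |
| Follow-up | No | Yes | V5; depends on the reading date |

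The two items that are masked do not define bone status. The two items that do are not named. Of these, the V1 imaging exists by visit order before either tracer is read. Follow-up might or might not be known, because the reading date is open.

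**Illustration of size.** The inputs below are assumptions, not protocol figures. Let a share c of the calls that disagree with the reference be revised because the reader knows part of it. An index with true value x is then reported as

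x + c(1 − x).

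Assume true sensitivity/specificity of 0.80/0.90 for 3PRGD2 and 0.85/0.65 for MDP.

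| c | 3PRGD2 sensitivity | 3PRGD2 specificity | MDP sensitivity | MDP specificity |
|---|---|---|---|---|
| 0.1 | 0.82 | 0.91 | 0.865 | 0.685 |
| 0.3 | 0.86 | 0.93 | 0.895 | 0.755 |
| 0.5 | 0.90 | 0.95 | 0.925 | 0.825 |

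For example, 0.80 + 0.3 × 0.20 = 0.86. Under this model each index rises for any c above zero and any x below one.

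**Effect on the comparison.** With the same c for both tracers, the assumed specificity gap of 0.90 − 0.65 = 0.25 is multiplied by (1 − c), giving 0.225, 0.175 and 0.125. If c differs, the gap need not shrink. With c = 0.5 for 3PRGD2 and 0.1 for MDP, it is 0.95 − 0.685 = 0.265, wider than 0.25. With those same two shares, sensitivity is reported as 0.90 against 0.865, although the assumed true order is 0.80 against 0.85. The direction of any bias in the comparison is therefore open.

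**Scale.** If the analysis is per patient and all 40 are evaluable (both assumptions), one revised call moves overall accuracy by 1/40 = 2.5 percentage points. It moves sensitivity or specificity by more, because each has a smaller denominator.

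**The case against.** The strongest reply is that silence is not exposure. The Methods section names two masked items and does not say that readers were shown anything else. Masking to history could also be meant to cover the earlier work-up. The full reference needs follow-up as well as imaging, so if the scans were read soon after acquisition it would not yet exist. De-identification and reading order are often left to a reading manual or the SAP, which is not at hand.

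Part of this stands. A reader might infer that the panel was in fact unmasked to the reference, or knew the follow-up. The documents support neither: they do not describe access to the imaging, and they do not date the reading. A reader might also infer that the bias narrows the difference between the tracers. That follows only if both tracers are affected equally, which nothing in the protocol establishes.

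The rest does not remove the point. The Flow Chart keeps medical history and the CT/MRI/PET row apart, so the broad meaning of history is at best uncertain, and later follow-up is hardly history. The protocol is also not silent on masking. It states a rule, and that rule names items that do not decide bone status. Knowing only the V1 imaging is enough to influence a reading, because that imaging can contribute to the reference.

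**Conclusion.** The point holds as a gap in the masking rule. The protocol does not state that readers are blind to the other imaging and the follow-up that set bone status, and the V1 imaging already exists when the tracers are read. A reading that follows the plan could therefore be made with knowledge of part of the reference, which risks raising the apparent sensitivity and specificity of each tracer. This is a risk and not a demonstrated effect. Its size cannot be found from the documents, and neither can its direction for the comparison of 3PRGD2 with MDP. The tabulated values rest wholly on assumed accuracies and assumed revision shares.

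One limit remains. The reference list also includes SPECT. If that means one of the index scans, masking readers to other imaging would not by itself make the index test and the reference independent. The protocol does not say whether it does.

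**What to change.** Replace the masking clause in Methods with wording such as: *readers are masked to clinical history, pathology, all other imaging (CT, MRI, PET-CT) with its reports, and follow-up; images are de-identified; bone calls are recorded and locked before the reference bone status is opened.*

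The cost is one sentence, minor de-identification work and a lockable reading form. No patient, scan or reader is added. The accuracy figures may come out slightly lower. If readings have already been made without these safeguards, the report should state what the panel had access to. A bias of this kind cannot be removed afterwards without a new masked reading.
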